### Secondary outcome

2.5

Secondary outcomes will be assessed at baseline (T0), week 8 (T2), and week 26 (T3), unless otherwise specified. Pain intensity will be measured using the Numerical Rating Scale (NRS), ranging from 0 to 10, with higher scores indicating greater pain intensity. Depressive symptoms will be assessed using the Patient Health Questionnaire-9 (PHQ-9), and anxiety symptoms using the Generalized Anxiety Disorder-7 (GAD-7), with higher scores indicating more severe symptoms. Physical activity will be evaluated using the International Physical Activity Questionnaire–Short Form (IPAQ-SF). Sleep quality will be assessed using Athens Insomnia Scale, with higher scores indicating poorer sleep quality. Fear-avoidance beliefs related to physical activity will be measured using the Fear-Avoidance Beliefs Questionnaire–Physical Activity subscale (FABQ-PA), and pain catastrophizing will be assessed using the Pain Catastrophizing Scale (PCS), with higher scores indicating greater fear-avoidance beliefs and pain catastrophizing, respectively. Work productivity and activity impairment will be evaluated using the Work Productivity and Activity Impairment questionnaire (WPAI), with higher percentages indicating greater impairment. Global improvement will be assessed at weeks 8 and 26 using a patient-reported global improvement measure, with higher scores indicating greater perceived improvement. Use of any treatments, including pharmacological and non-pharmacological therapies, will be recorded at baseline, week 8, and week 26. System usability will be assessed in the intervention group only using the System Usability Scale (SUS) at week 8, with higher scores indicating better usability. Patient satisfaction will be assessed in both groups at weeks 4, 8 and 26.

### Safety outcomes

2.6

Adverse events will be monitored at each participant contact. VR-related symptoms, including dizziness, nausea and vomiting, headache, eye soreness, and falls, will be recorded. These symptoms are expected to be mostly mild and transient. If a participant experiences a fall or significant discomfort, the intervention session will be paused or discontinued as appropriate. Serious adverse events will be reported to the Data and Safety Monitoring Committee within 24 h.

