Participants assigned to the intervention group will attend one facilitator-guided, in-clinic VR-MBCT session per week for 8 weeks, with each session lasting approximately 30 min. Between sessions, they will complete audio-guided mindfulness practice at home three times per week, with each practice lasting 20–30 min. No VR equipment will be used for home practice. Each in-clinic session will be automatically generated by the system and facilitated by trained research staff, who will assist with equipment setup, safety monitoring, and procedural guidance. The 8-week progressive curriculum is summarized in Supplementary Table S1 and includes the following themes: automatic pilot and awareness, including body scan and mindful breathing; body scan and movement repertoire, including cat-cow exercises and visual feedback; mindful movement and graded exposure, including system-adjusted spinal and core exercises; responding rather than reacting, including the ABC model and urge surfing; cognitive defusion, including thought replacement exercises; self-compassion, including acceptance narratives and posture transitions; relapse prevention and self-care, including compassionate letter writing and loving-kindness meditation; and maintenance planning and real-world transfer, including system- guided training and individualized maintenance planning. A detailed breakdown of weekly themes, VR core scenes, and key teaching points is provided in Supplementary Table S1.

System-generated data will include training duration, module completion, and pause events. Self-reported data, including ABC practice logs and scene preferences, as well as anxiety scores assessed using a 0–10 visual analogue scale before and after each VR session, will be collected through the system interface. Research staff will conduct weekly telephone follow-ups to promote participant adherence. If a participant misses a VR session, a brief motivational interview will be conducted to identify barriers and encourage continued participation.

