Participants in the control group will receive standard clinical care, including pharmacological treatment, such as analgesics, and physical therapy, such as extracorporeal shock wave therapy. They will not receive structured VR training during the initial 8-week study period. After completing the 6-month follow-up assessment, participants in the control group may receive the same 8-week VR-MBCT program according to their preferences. Group allocation will remain concealed from outcome assessors and statisticians until study completion.

Randomization will be conducted before the study begins by an independent researcher using a computer-generated randomization sequence with stratified block randomization according to study center and age (≥60 years or <60 years), using block sizes of 2 and 4. Group assignments will be concealed using sequentially numbered, sealed, opaque envelopes, which will only be opened after the participant is enrolled and assigned. Due to the nature of the VR-based intervention, blinding of participants and intervention therapists is not feasible. However, outcome assessors and statisticians will remain blinded to group allocation throughout the study to minimize detection bias. The schedule for patient enrollment, study interventions, and outcome assessments will adhere to the SPIRIT statement (Supplementary Table S2).

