### Data collection and monitoring

2.9

Patient information will be collected from electronic medical records and baseline self-report questionnaires. Variables will include age, sex, body mass index, education level, employment status, pain duration, comorbidities, current treatment use, expectations for pain improvement, and other relevant clinical characteristics. Significant life events, such as major illness, accidents, bereavement, or changes in employment status, will also be recorded. As all participants will be recruited from outpatient clinics, hospital admission will not be required. Follow-up data will be collected through in-person visits at weeks 4 and 8 and telephone interviews at week 26, and then entered into a secure electronic data capture system.

To ensure data accuracy and integrity, all data will be independently double-entered by two trained research coordinators. Discrepancies will be resolved through discussion or consultation with the principal investigator. Regular monitoring and audits will be conducted by an independent data quality supervisor to verify source documents against entered data. Research staff involved in data collection will receive standardized training in case report form completion and protocol adherence before trial initiation. A dedicated Data Monitoring Committee will oversee data quality, Good Clinical Practice compliance, and protocol deviations.

Serious adverse events, regardless of their relationship to the VR intervention, including dizziness, headache, falls, syncope, nausea, or vomiting, will be reported promptly to the principal investigator. Appropriate measures will be taken to ensure participant safety. Serious adverse events will also be reported to the Data Monitoring Committee within 24 h for assessment and, if necessary, modification or discontinuation of the study protocol.

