Missing outcome data will initially be handled under a missing-at-random assumption using likelihood-based estimation within the GEE framework and adjustment for predictors of missingness. Sensitivity analyses will be performed using multiple imputation methods and per-protocol analyses to evaluate the robustness of the findings under different missing-data assumptions.

Safety analyses will include all participants who received at least one intervention session. Adverse events will be summarized descriptively and compared between groups using chi-square tests or Fisher exact tests, as appropriate.

All analyses will be performed using R software (R Foundation for Statistical Computing, Vienna, Austria) or SPSS software (IBM Corp., Armonk, NY, USA).

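### Adverse events are collected at each contact, but the VR arm has several times as many study contacts as controls, so the planned between-group test can be inflated against VR

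*Protocol article*

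**What the plan says.** Four statements in the protocol article combine here.

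- **Detection rule (2.6, Safety outcomes).** "Adverse events will be monitored at each participant contact". The same section says of the VR-related symptoms: "These symptoms are expected to be mostly mild and transient".
- **VR arm contacts (2.8, Study interventions).** Participants in this arm "will attend one facilitator-guided, in-clinic VR-MBCT session per week for 8 weeks", with research staff present who also monitor safety. The section adds: "Research staff will conduct weekly telephone follow-ups to promote participant adherence".
- **Contacts shared by both arms (2.9, Data collection and monitoring).** "Follow-up data will be collected through in-person visits at weeks 4 and 8 and telephone interviews at week 26". For controls, 2.8 describes standard care and says "They will not receive structured VR training during the initial 8-week study period"; it states no further study contact for them.
- **Analysis (2.11, Statistical analysis).** "Adverse events will be summarized descriptively and compared between groups using chi-square tests or Fisher exact tests, as appropriate".

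The article does not say that the between-group comparison is limited to events collected on a schedule common to both arms. The limitations paragraph in the Discussion does not mention unequal ascertainment.

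**The concern.** A chi-square or Fisher test of adverse event proportions assumes that an event of a given kind is equally likely to be recorded in either arm. Under the stated rule it is not. A VR participant with a headache or a spell of dizziness is seen by staff that day or within about a week. A control with the same symptom may have to remember it for up to four weeks. Headache, dizziness, nausea and falls also occur without VR, so controls have a background rate that can be under-recorded.

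Evaluating safety is a stated aim of the trial. A significant excess in the VR arm could not be separated into true risk and extra surveillance, and the likely direction of the error is against the intervention. Efficacy analyses and the sample size are unaffected.

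**Working it through.** The article gives no contact count, no expected adverse event rate and no power for safety, so there is no planned figure to reproduce. The check has two steps.

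**Step 1: count study contacts in the first 8 weeks, from 2.8 and 2.9.**

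| Reading | VR arm | Control arm |
|---|---|---|
| Sessions and assessments, calls ignored | 8 + 2 = 10, or 8 if the week 4 and 8 assessments coincide with sessions | 2 |
| Weekly calls counted, VR arm only | 8 + 8 + 2 = 18, or 16 if they coincide | 2 |
| Weekly calls to both arms (not stated) | 16 to 18 | 8 + 2 = 10 |

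The ratio is 4 to 5 on the first reading, 8 to 9 on the second and 1.6 to 1.8 on the third. That the calls go only to the VR arm is an inference: they are described among the intervention-arm procedures, serve adherence, and are followed directly by what happens when a VR session is missed.

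**Step 2: what unequal spacing can do when the true risk is equal.** All inputs here are assumptions except the 107 per arm (2.10) and the contact spacing.

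- True 8-week risk of any event is 20% in both arms, so the weekly risk is w = 1 − (1 − 0.20)^(1/8) = 0.0275.
- An event in the week of a contact is recorded with probability 0.9. Each week of delay multiplies this by a retention factor d.
- VR participants are asked every week. Controls are asked at weeks 4 and 8, so their delays are 3, 2, 1 and 0 weeks, twice.
- P(at least one event recorded) = 1 − ∏(1 − w × 0.9 × d^L), taken over the 8 weeks, where L is the delay to the next contact.

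VR arm: 1 − (1 − 0.0275 × 0.9)^8 = 18.2%, whatever d is.

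Control arm at d = 0.7: the recording probabilities are 0.309, 0.441, 0.630 and 0.900. The product of the four terms is about 0.939, and 1 − 0.939² is about 11.9%.

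| d per week | VR recorded | Control recorded | Spurious RR | Chi-square rejection rate, 107 per arm |
|---|---|---|---|---|
| 1.0 | 18.2% | 18.2% | 1.00 | 5.0% |
| 0.9 | 18.2% | 15.8% | 1.15 | 7.5% |
| 0.7 | 18.2% | 11.9% | 1.53 | 25% |
| 0.5 | 18.2% | 8.9% | 2.03 | 52% |

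The relative risk depends little on the assumed true risk. At d = 0.7 and true risks from 10% to 40% it runs from 1.55 to 1.47, while the rejection rate rises from 15% to 46%.

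The model uses one VR contact per week, so it does not need the adherence calls. If controls were also called weekly and asked about adverse events, both arms would be asked every week and the model would give no difference. What would then remain is direct observation by staff at the VR sessions.

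**The case against.** The strongest objection is to the size. A reader might take the contact ratio as the size of the bias, or assume a fixed chance of recording an event at each contact, and conclude that the VR arm is bound to show a many-fold excess and that any safety finding would be an artefact. The article does not support this. An adverse event question normally covers the time since the last contact, so one control visit can capture about four weeks. A fixed chance per contact assumes that nothing is remembered between contacts. It also treats a session and a call in the same week as independent detections. With full recall the bias is zero. This part of the objection stands.

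It also stands that the calls are not expressly limited to the VR arm, that they are made for adherence so their yield of adverse events is unknown, and that the term contact is undefined, while controls also attend usual care.

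A further objection is that the event form and recall window belong in the full protocol, case report form or SAP, none of which is shown. That is fair: the absence of a checklist from an article does not show that none exists. But the point rests on what the article does state, namely the detection rule, the schedules and the between-group test. An analysis plan alone could not repair the comparison if controls were never asked comparable questions.

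Finally, closer monitoring of the exposed arm is ordinary safety practice, and safety has no hypothesis or decision rule here. That limits the consequence but does not make the planned test interpretable. Separately, the safety set in 2.11, read literally, requires at least one intervention session and so would exclude controls. That needs its own correction and does not resolve this point.

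**Conclusion.** The concern holds in a limited form. Followed as written, the plan gives unequal ascertainment: at least 8 to 10 study contacts against 2 in 8 weeks, and 16 to 18 against 2 if the calls are counted as VR-only. It then applies a test that assumes equal ascertainment. The comparison can be inflated against VR, to an unknown degree. The illustration runs from no bias with perfect recall to a spurious relative risk of about 1.15, 1.5 or 2.0 at weekly retention of 0.9, 0.7 or 0.5, given a true risk of 20% in both arms. The retention factors, the 0.9 capture probability and the true risk are assumptions. The contact spacing comes from the article, apart from the reading that controls receive no weekly calls. It is worth correcting because safety is a stated aim and the remedy is cheap, but it does not touch the efficacy conclusions.

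**What to change.** Ask both arms the same short adverse event checklist (falls, dizziness, headache, nausea or vomiting, eye soreness, other), with the same recall period, at the existing week 4, 8 and 26 assessments. Base the between-arm comparison on those checklist data only. Report every event noted at VR sessions or calls in full, including falls and all serious events, but descriptively for the VR arm, for example as events per session. State in 2.8 whether the weekly calls go to one arm or both.

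The cost is one form and a few lines in the protocol and SAP; no visit is added. There are three downsides to state openly. The comparison will rest on recall, so some mild events will be missed in both arms. Participants know their allocation, so differential reporting remains possible. And because data collection is described as ongoing, the checklist will exist only for assessments made after it is introduced, so that date should be recorded and reported.

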### Randomization and blinding

2.7

Randomization will be performed using a computer-generated sequence with a 1:1 allocation ratio. Stratified block randomization will be applied according to study center and age (≥60 years or <60 years), with block sizes of 2 and 4. Allocation concealment will be ensured using sequentially numbered, sealed, opaque envelopes. Due to the nature of the intervention, participants and VR therapists can not be blinded. However, outcome assessors and statisticians will remain blinded to group allocation throughout the study.

### Study interventions

2.8

The VR-MBCT program was specifically developed for patients with chronic non-specific low back pain. All participants followed the same standardized 8-week MBCT sequence. Condition-specific adaptations included VR scenarios addressing pain-related bodily sensations, thoughts, emotions, and movement avoidance; mindful movement combined with low-back-friendly rehabilitation exercises; and real-time feedback on posture and movement amplitude. Exercise difficulty could be adjusted within prespecified limits according to performance, whereas the therapeutic content and progression remained standardized.

The intervention will be delivered through a VR-MR system co-developed by the research team and Hangzhou Yijian Technology Co., Ltd. The system consists of a PICO Ultra VR-MR headset, which provides immersive mixed-reality experiences, and a DM-TG01A motion capture camera, which enables real-time tracking of participants' movements and postures, as well as feedback and correction through the VR headset. All equipment will be provided to participants free of charge.

Participants assigned to the intervention group will attend one facilitator-guided, in-clinic VR-MBCT session per week for 8 weeks, with each session lasting approximately 30 min. Between sessions, they will complete audio-guided mindfulness practice at home three times per week, with each practice lasting 20–30 min. No VR equipment will be used for home practice. Each in-clinic session will be automatically generated by the system and facilitated by trained research staff, who will assist with equipment setup, safety monitoring, and procedural guidance. The 8-week progressive curriculum is summarized in Supplementary Table S1 and includes the following themes: automatic pilot and awareness, including body scan and mindful breathing; body scan and movement repertoire, including cat-cow exercises and visual feedback; mindful movement and graded exposure, including system-adjusted spinal and core exercises; responding rather than reacting, including the ABC model and urge surfing; cognitive defusion, including thought replacement exercises; self-compassion, including acceptance narratives and posture transitions; relapse prevention and self-care, including compassionate letter writing and loving-kindness meditation; and maintenance planning and real-world transfer, including system- guided training and individualized maintenance planning. A detailed breakdown of weekly themes, VR core scenes, and key teaching points is provided in Supplementary Table S1.

System-generated data will include training duration, module completion, and pause events. Self-reported data, including ABC practice logs and scene preferences, as well as anxiety scores assessed using a 0–10 visual analogue scale before and after each VR session, will be collected through the system interface. Research staff will conduct weekly telephone follow-ups to promote participant adherence. If a participant misses a VR session, a brief motivational interview will be conducted to identify barriers and encourage continued participation.

Participants in the control group will receive standard clinical care, including pharmacological treatment, such as analgesics, and physical therapy, such as extracorporeal shock wave therapy. They will not receive structured VR training during the initial 8-week study period. After completing the 6-month follow-up assessment, participants in the control group may receive the same 8-week VR-MBCT program according to their preferences. Group allocation will remain concealed from outcome assessors and statisticians until study completion.

Randomization will be conducted before the study begins by an independent researcher using a computer-generated randomization sequence with stratified block randomization according to study center and age (≥60 years or <60 years), using block sizes of 2 and 4. Group assignments will be concealed using sequentially numbered, sealed, opaque envelopes, which will only be opened after the participant is enrolled and assigned. Due to the nature of the VR-based intervention, blinding of participants and intervention therapists is not feasible. However, outcome assessors and statisticians will remain blinded to group allocation throughout the study to minimize detection bias. The schedule for patient enrollment, study interventions, and outcome assessments will adhere to the SPIRIT statement (Supplementary Table S2).

### Data collection and monitoring

2.9

Patient information will be collected from electronic medical records and baseline self-report questionnaires. Variables will include age, sex, body mass index, education level, employment status, pain duration, comorbidities, current treatment use, expectations for pain improvement, and other relevant clinical characteristics. Significant life events, such as major illness, accidents, bereavement, or changes in employment status, will also be recorded. As all participants will be recruited from outpatient clinics, hospital admission will not be required. Follow-up data will be collected through in-person visits at weeks 4 and 8 and telephone interviews at week 26, and then entered into a secure electronic data capture system.

To ensure data accuracy and integrity, all data will be independently double-entered by two trained research coordinators. Discrepancies will be resolved through discussion or consultation with the principal investigator. Regular monitoring and audits will be conducted by an independent data quality supervisor to verify source documents against entered data. Research staff involved in data collection will receive standardized training in case report form completion and protocol adherence before trial initiation. A dedicated Data Monitoring Committee will oversee data quality, Good Clinical Practice compliance, and protocol deviations.

Serious adverse events, regardless of their relationship to the VR intervention, including dizziness, headache, falls, syncope, nausea, or vomiting, will be reported promptly to the principal investigator. Appropriate measures will be taken to ensure participant safety. Serious adverse events will also be reported to the Data Monitoring Committee within 24 h for assessment and, if necessary, modification or discontinuation of the study protocol.

